### **Structure and implementation**

The JADE Program was developed and administered by the Asia Diabetes Foundation (ADF, [www.adf.org.hk](http://www.adf.org.hk)), a charitable organization registered under the Hong Kong Government and governed by the Chinese University of Hong Kong Foundation. In this investigator-initiated project, the ADF will provide the portal support and project management including portal training, database management and analysis. All data are collected on an anonymous basis which will contribute to a DKD Registry steered by international and regional experts with representatives from the sponsor for analysis, reporting and communication purposes. A committee consisting of nephrologists, diabetologists, cardiologists, epidemiologists and biostatisticians will meet regularly to ascertain the outcome measures based on narratives and supporting data. Members of the ADF team will visit the sites at least once a year to review the progress of the study while the JADE portal will be used to monitor the speed of patient recruitment and quality of data entry, followed by teleconference as and when required. All investigators and steering committee members will meet at least 3 times during the 1.5-year study period, i.e. at commencement, half way and completion. At least 1 nurse and 1 doctor responsible for study implementation will visit Hong Kong to attend a 1-day training workshop to familiarize themselves with the JADE portal and the workflow of implementing structured and team-based care.

### **Sample size estimation**

Most surveys in developing areas (Asia, East Europe and South America) show that only 20-30% of patients were treated with statins or RAS inhibitors or attained 1 of the 3 ABC goals (A1c<7%, BP<130/80 mmHg and LDL-C<2.6 mmol/l) and only 3-10% attained multiple treatment

goals. Based on our experiences using the JADE Program which has enrolled more than 30,000 patients since its launch in 2007, the organization, presentation and communication of data in an easy-to-read format has empowered patients to improve compliance with better physical and psychological health.

The power analysis and sample size estimation (Appendices 3 and 4) was conducted using PASS 11 (NCSS, LLC. Kaysville, Utah, USA. [www.ncss.com](http://www.ncss.com)). We estimated the rates of attainment of multiple treatment targets to be 10%, 20% and 30% in the UC, EC and TEC groups respectively. A sample size of 1000 patients in each of the 3 groups will have >95% power to test the primary hypothesis using a 2-sided likelihood ratio test and taking into consideration of multiple comparisons (type I error set at 1%). We further estimated that patients in the UC group will at least have an event rate of 5% per year, and EC group will have a 37% risk reduction (i.e., HR=0.63). A sample size of 2000 in total (1000 in the UC group and 1000 in the EC group) will have 80% power to confirm the effect size at an alpha of 0.05 assuming a yearly attrition rate of 20% in each group, half year for enrolment and 1 year for follow up and no switch in intervention between groups. For the comparison of the TEC with the UC group, we take multiple comparisons into consideration, i.e., type I error at 2.5%. A sample size of 2000 in total (1000 in the UC group and 1000 in the TEC group) will have 80% power to confirm the effect size of 50% risk reduction (HR=0.50) assuming an attrition rate of 20% in each group, half year for enrolment and 1 year for follow up and no switch in intervention between groups. Thus, a total of 3000 patients, 1000 in each group, is needed to achieve the effect sizes with 80% power and taking into consideration of multiple comparisons.

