## **Setting**

All patients will be recruited from high volume clinics in Asia led by diabetologists or nephrologists or cardiologists or internists. Each centre will consecutively recruit 300 patients with DKD and randomize them to UC (n=100), EC (n=100) or TEC (n=100) groups. After giving written informed consent, they will be randomized using sealed envelope, opened by an independent personnel, containing randomly generated computer codes for group assignment. All patients will undergo comprehensive assessments including examination of eye and feet as well as collection of blood and urine samples at baseline and 1 year later in accordance to international recommendations. Each patient will be followed up at least for 1 year and assuming half year of set up and patient recruitment, the project will last for 1.5 years. At the end of 1.5 years, the clinical outcomes of all enrolled patients will be ascertained by telephone contact within 1 month of the due date of repeat assessment of the last recruited patient.

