## Summary Statements

A two-sided logrank test with an overall sample size of 2000 subjects (1000 in the control group and 1000 in the treatment group) achieves 99.9% power at a 0.050 significance level to detect a hazard ratio of 0.4000 when the control group hazard rate is a hazard ratio of 0.0500. The study lasts for 3 time periods of which subject accrual (entry) occurs in the first time period. The proportion dropping out of the control group is 0.2000. The proportion dropping out of the treatment group is 0.2000. The proportion switching from the control group to another group with a hazard rate equal to the treatment group is 0.0000. The proportion switching from the treatment group to another group with a hazard rate equal to the control group is 0.0000.

Logrank Test Power Analysis

Chart Section

[figure not shown]

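### The 80% power stated for EC versus UC on clinical events does not follow from the protocol's own assumptions; on its half-year enrolment and one-year follow-up the power is about 56–57%

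*Protocol*

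**What the plan says.** The Sample size estimation section gives two power statements for clinical events. For EC versus UC, it assumes that "patients in the UC group will at least have an event rate of 5% per year" and that the EC hazard ratio is 0.63. It concludes that 1000 patients per arm "will have 80% power to confirm the effect size at an alpha of 0.05 assuming a yearly attrition rate of 20% in each group", with half a year of enrolment, one year of follow-up and no crossover. For TEC versus UC, it claims 80% power for a hazard ratio of 0.50 at a type I error of 2.5%, with the same numbers and timeline. It then says that 3000 patients give 80% power for these effect sizes.

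The Setting section gives the same timeline: "assuming half year of set up and patient recruitment, the project will last for 1.5 years".

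The text refers to Appendix 4 for the calculation. In the row for hazard ratio 0.63, that output shows power 0.7971 and 148.4 events (90.3 control, 58.1 treatment) for 1000 per arm at two-sided alpha 0.05. Accrual time over total time is 1 / 3, the control hazard is 0.05 and the loss is 0.20. Its summary statement reads: "The study lasts for 3 time periods of which subject accrual (entry) occurs in the first time period". Its report definitions put the hazard and the loss on the same time-period scale as accrual and total time.

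**The concern.** The rates and the durations in Appendix 4 share one time unit, and no choice of unit agrees with the text:

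| Period read as | Accrual / total | UC events | Loss | Agrees with the text? |
|---|---|---|---|---|
| One year | 1 / 3 years | 5% per year | 20% per year | Rates yes, timeline no |
| Half a year | 0.5 / 1.5 years | about 10% per year | 36% per year (1 − 0.8²) | Timeline yes, rates no |

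So the 80% belongs to a different study from the one described: one twice as long, or one with twice the event rate.

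Reducing clinical outcomes is a stated objective, and the Statistical analysis section plans a number needed to treat for EC separately. The event calculations also form part of the stated justification for 3000 patients. If the figure stands, a non-significant EC result on events could be read as coming from an 80%-powered comparison when the design offers little better than an even chance of detecting the assumed effect.

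**Working it through.** **Inputs, from the Sample size estimation section:** 1000 per arm; UC hazard h = 0.05 per year; EC hazard 0.63 × 0.05 = 0.0315; loss 20% per year, so l = −ln 0.8 = 0.2231; two-sided alpha 0.05 (z = 1.960). Enrolment is taken as uniform, as in Appendix 4, and event and loss times as exponential.

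**Formulas.** For potential follow-up u uniform on [a, b]:

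- Events per 1000 = 1000 × h/(h+l) × [1 − M], where M is the mean of exp(−(h+l)u) = [exp(−(h+l)a) − exp(−(h+l)b)] / [(h+l)(b−a)].
- Power with E total events and equal arms: Schoenfeld Φ(½√E·|ln HR| − 1.960); Freedman Φ(√E·(1−HR)/(1+HR) − 1.960).

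**Step 1: reproduce Appendix 4** (accrual 1, total 3, so u runs from 2 to 3).

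- Control: 0.1831 × (1 − 0.5067) × 1000 = 90.3.
- Treatment: 0.1237 × (1 − 0.5305) × 1000 = 58.1.
- Total 148.4, identical to the appendix.
- Power: Schoenfeld Φ(2.814 − 1.960) = 0.803; Freedman Φ(2.765 − 1.960) = 0.790. A Lakatos-type log-rank calculation gives 0.792 and a simulation of 4000 trials gives 0.800. The appendix says 0.7971, so the method reproduces the plan's figure.

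**Step 2: use the timeline in the text** (accrual 0.5, total 1.5 years, so u runs from 1 to 1.5).

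- Control: 0.1831 × (1 − 0.7113) × 1000 ≈ 52.8.
- Treatment: 0.1237 × (1 − 0.7279) × 1000 ≈ 33.7.
- Total 86.5.
- Power: Schoenfeld Φ(2.149 − 1.960) = 0.575; Freedman Φ(2.111 − 1.960) = 0.560; Lakatos-type 0.561; simulation 0.566.

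**Step 3: the half-year reading.** Keep accrual 1 and total 3 half-year periods, but put the text's yearly rates on that scale: hazard 0.025 and loss 1 − √0.8 per period. This again gives 52.8 + 33.7 = 86.5 events and the same power.

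**Step 4: what 80% would take.** With z = 0.842 for power, Schoenfeld needs 4(1.960 + 0.842)²/(ln 0.63)² ≈ 148 events and Freedman about 153. On the 1.5-year timeline this means any one of:

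- about 1,710 (Schoenfeld) to 1,770 (Freedman) patients per arm;
- a UC hazard of about 8.7% to 9.0% per year;
- a hazard ratio of about 0.53 to 0.54 in place of 0.63.

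**Step 5: sensitivity at hazard ratio 0.63.**

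| Variant of the 0.5 / 1.5-year design | Power |
|---|---|
| No loss at all | 0.62–0.63 |
| 5% read as a yearly risk (hazard −ln 0.95) | 0.57–0.59 |
| Exactly one year of follow-up per patient | 0.48–0.50 |

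**Step 6: cross-check without Appendix 4.** The text gives TEC versus UC the same 80% with the same numbers and timeline. On 0.5 / 1.5 years, hazard ratio 0.50 and alpha 0.025, the expected events are 52.8 + 26.8 ≈ 79.7 and power is 0.77 to 0.80, so that claim is roughly right. On the appendix's 1 / 3 timeline it would be 0.95 to 0.96. Within either timeline, the two 80% figures cannot both hold.

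**The case against.** Four points can be made for the plan.

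1. *Appendix 4 never says that a period is a year.* Its ratio 1 / 3 equals 0.5 / 1.5, so the slip may be yearly rates entered as half-yearly rates. That is possible, and the document does not settle which input was wrong. Step 3 shows that either correction ends at the same power.

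2. *The 5% is a minimum.* At UC hazards of 6%, 7%, 8% and 9% per year, power is about 0.64–0.65, 0.70–0.72, 0.76–0.77 and 0.80–0.81. This stands as a qualification: 56–57% is the power at the protocol's minimum rate. It does not support the text, which claims 80% at that rate and offers no basis for a rate near 9%.

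3. *Events are not the primary endpoint.* Correct. The secondary outcome listed under Outcome measures even compares patients by target attainment, not by arm. Primary power is untouched: Appendix 3 shows at least 0.98 for every pairwise contrast at 800 per arm. This limits the consequences but does not make the stated power true.

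4. *TEC versus UC is roughly right.* Also correct, so the shortfall is specific to EC versus UC. The closing sentence covers both comparisons and therefore still fails.

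**Conclusion.** The stated 80% power for EC versus UC on clinical events is wrong. With the protocol's own inputs (1000 per arm, 5% per year in UC, hazard ratio 0.63, 20% yearly loss, half a year of enrolment and one further year, two-sided 0.05), about 86.5 events are expected where about 148 to 153 are needed, and power is about 56–57%. The result rests on constant hazards, uniform enrolment and no crossover, as in Appendix 4, whose event counts the same calculation reproduces to the decimal. It does not depend on how the appendix's time period is read. A true UC rate above the 5% minimum would raise the power, and about 8.7–9.0% per year would be needed to reach 80%. The joint claim that 3000 patients give 80% power for both event comparisons is false because of EC versus UC alone.

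**What to change.** - Rerun Appendix 4 with accrual 0.5 and total time 1.5 years, hazard 0.05 per year and loss 0.20 per year, and state the time unit in the output.
- In Sample size estimation, restate EC versus UC as about 56–57% power at hazard ratio 0.63 and a 5% yearly UC rate, with a detectable hazard ratio of about 0.53 at 80% power. If a higher UC rate is thought likely, give the power at that rate beside it and say what supports it.
- Add the missing run for TEC versus UC (hazard ratio 0.50, alpha 0.025): every row of Appendix 4 uses alpha 0.05. Quote what it gives, about 77–80%.
- Replace the closing sentence so that it no longer claims 80% power for both event comparisons. The 3000 patients can be justified by the primary endpoint, which keeps more than 95% power.

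The cost is two software runs and a wording change. Enrolment, visits and treatment are untouched. The stated event power becomes less favourable.

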### **Statistical analysis**

All analyses will be performed using the Statistical Program for Social Sciences (SPSS). All data will be expressed as mean±SD or median (interquartile range) as appropriate. Skewed data will be logarithmically transformed. Analysis of variance, student's t test and Fisher's exact-test will be used for comparisons amongst the UC, EC and TEC groups, as appropriate. The Kaplan Miere estimator will be used to demonstrate the cumulative incidence of first diabetes-related event while Cox model with adjustment for covariables at baseline and during follow-up will be used to check their contributions to the observed risk reductions. A p-value <0.05 (2-sided) will be considered significant. Number needed to treat (NNT) for prevention of an event by the EC and TEC group will be calculated separately using survival functions.

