## Summary Statements

Group sample sizes of 500 in group one and 500 in group two achieve 86% power to detect a difference between the group proportions of -0.1000. The proportion in group one (the treatment group) is assumed to be 0.3000 under the null hypothesis and 0.2000 under the alternative hypothesis. The proportion in group two (the control group) is 0.3000. The test statistic used is the two-sided Likelihood Ratio test. The significance level of the test was targeted at 0.0100. The significance level actually achieved by this design is NA.

8/12/2012 3:31:34 PM 2

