## Summary Statements

Group sample sizes of 500 in group one and 500 in group two achieve 97% power to detect a difference between the group proportions of -0.1000. The proportion in group one (the treatment group) is assumed to be 0.2000 under the null hypothesis and 0.1000 under the alternative hypothesis. The proportion in group two (the control group) is 0.2000. The test statistic used is the two-sided Likelihood Ratio test. The significance level of the test was targeted at 0.0100. The significance level actually achieved by this design is NA.

8/12/2012 3:30:31 PM

2

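### The primary comparisons are planned at 1% and TEC vs UC events at 2.5% to allow for multiplicity, but the analysis section declares any two-sided p<0.05 significant

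*Protocol*

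**What the plan says.** **Primary outcome.** Sample size estimation assumes "rates of attainment of multiple treatment targets to be 10%, 20% and 30% in the UC, EC and TEC groups respectively". It states that "A sample size of 1000 patients in each of the 3 groups will have >95% power to test the primary hypothesis" with a two-sided likelihood ratio test, "taking into consideration of multiple comparisons (type I error set at 1" per cent). Appendix 3 has three runs, one for each pair of arms, and each summary statement says "The significance level of the test was targeted at 0.0100".

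**Events.** The same section plans EC vs UC at an alpha of 0.05. It continues: "For the comparison of the TEC with the UC group, we take multiple comparisons into consideration, i.e., type I error at 2.5" per cent. It concludes that 3000 patients are enough once multiple comparisons are allowed for. Every run in Appendix 4 uses 0.05; none uses 0.025.

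**Decision rule.** Statistical analysis names analysis of variance, t tests and Fisher's exact test for comparing the three groups as appropriate. It then gives one threshold for everything: "A p-value <0.05 (2-sided) will be considered significant". It does not mention the 1% or 2.5% level, an overall test that must succeed first, or an order of testing.

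**The concern.** The protocol allows for multiple comparisons when it sizes the trial and drops that allowance when it states how results will be judged. This is a conflict between two statements in the protocol, so it is more than a detail left to the statistical analysis plan.

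The practical risk is a result in the gap between the rules. A primary pairwise p-value between 0.01 and 0.05 fails the level on which the trial was sized but passes the stated analysis rule. The same holds for a TEC vs UC event p-value between 0.025 and 0.05. With both rules in the protocol, the conclusion could depend on which section is cited after the data are seen.

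For events there is a second gap. The planned levels, 0.05 and 0.025, add to more than 5% unless one test depends on the other, and no dependence is stated.

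**Working it through.** **1. Reproduce Appendix 3.** Inputs: 10%, 20% and 30% attainment, two-sided alpha 0.01 (z = 2.5758), n per arm. With p̄ the mean of the two proportions,

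power = Φ{ [ |p1−p2|·√n − z·√(2p̄(1−p̄)) ] / √(p1(1−p1)+p2(1−p2)) }.

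- 10% vs 20%, n=500: (2.2361 − 2.5758×0.5050)/0.5000 = 1.871, so power is 0.9693. Appendix 3 prints 0.9693, and its summary reads "Group sample sizes of 500 in group one and 500 in group two achieve 97% power".
- 20% vs 30%, n=500: (2.2361 − 2.5758×0.6124)/0.6083 = 1.083, so power is 0.8606. Appendix 3 prints 0.8606 ("Group sample sizes of 500 in group one and 500 in group two achieve 86% power").

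The planning figures are therefore right, and they belong to alpha 0.01.

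**2. Primary power at 1000 per arm.**

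| Pair | alpha 0.01 | alpha 0.05 |
|---|---|---|
| 10% vs 20% | 0.9999 | >0.9999 |
| 20% vs 30% | 0.9954 | 0.9994 |

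The claim of more than 95% power holds at 0.01. Moving to 0.05 raises power slightly. At 800 per arm, Appendix 3 itself gives 0.9801 for 20% vs 30% at 0.01.

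**3. Family-wise error, primary.** Assume that all three arms are equal, that arm sizes are equal, and that the three pairs are tested with no gate. Each pairwise statistic is (Zi − Zj)/√2 with independent standard normal Z. The family-wise error is the probability that at least one exceeds its critical value in absolute size.

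- Each pair at 0.05: about 12.2% (Bonferroni bound 3×0.05 = 15%).
- Each pair at 0.01: about 2.7% (bound 3×0.01 = 3%).

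The ratio is 12.2/2.7, or about 4.5.

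**4. Family-wise error, events.** Two comparisons share the UC arm, so the statistics have correlation 0.5. With neither test conditional on the other:

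| EC vs UC | TEC vs UC | Bound | Family-wise error |
|---|---|---|---|
| 0.05 | 0.05 (analysis rule) | 10% | about 9% |
| 0.05 | 0.025 (planning) | 7.5% | about 6.9% |
| 0.025 | 0.025 | 5% | about 4.6% |

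**5. The planned event levels with an order.** Test TEC vs UC at 0.025 and go on to EC vs UC at 0.05 only if it succeeds. If both nulls are true, or only the TEC null, a false claim needs a false TEC rejection or follows one: at most 2.5%. If only the EC null is true, the error is at most 5%. So 5% holds in every case.

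**6. Event power for EC vs UC.** Appendix 4 gives 148.4 events at HR 0.63. Schoenfeld: Φ(½·√148.4·|ln 0.63| − z) = Φ(2.814 − z). Freedman: Φ(√148.4·0.37/1.63 − z) = Φ(2.765 − z).

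- alpha 0.05 (z = 1.960): 0.80 (Schoenfeld) and 0.79 (Freedman), against 0.7971 printed.
- alpha 0.025 (z = 2.241): 0.72 and 0.70.

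**The case against.** The strongest reply is that the protocol does not say that three ungated pairwise tests will be run. With three arms, an overall test at 0.05 followed by pairwise tests at 0.05 holds the family-wise error within one outcome at 5% (4.98% in a simulation of 2,000,000 draws). A separate analysis plan may specify this. That stands as a limit on the 12.2%, which is the error of the ungated reading. It does not remove the conflict, because the section states no gate and its blanket threshold contradicts the 1% level.

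Three further points stand:

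- A reader might infer that planned power is lost. It is not: a looser threshold raises power, and for EC vs UC events planning and analysis use the same 0.05.
- A reader might infer that 5% with 2.5% can never be a valid pair of levels. It can be, if TEC vs UC is tested first and gates EC vs UC. What is missing is the order.
- The listed secondary outcome compares patients by target attainment, not by arm. The arm comparisons of events are nonetheless what the sample size section powers, and the analysis section computes numbers needed to treat for EC and TEC.

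It can also be said that, at the assumed rates, every primary pair has over 99% power at 1%, so the threshold would seldom decide the matter. That is true if the assumptions hold; the choice of threshold matters most when effects are smaller than assumed.

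**Conclusion.** The point holds as a contradiction about type I error. It affects the primary pairwise comparisons (1% planned, 5% stated for analysis) and TEC vs UC events (2.5% planned, 5% stated).

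On an ungated reading under the global null with equal arms, the family-wise error for the primary is about 12.2% instead of 2.7%. For the two event comparisons it is about 9% under the analysis rule, and about 6.9% under the planning levels if the tests are unconditional. The 12.2% covers target attainment only. The protocol also lists RAS inhibitor use under the primary outcome; if that is a second primary test, and independent of the first (an assumption), the figure becomes 1 − (1 − 0.122)² = 23%.

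A reader might also blame the alpha conflict for EC vs UC event power of about 45%. That figure combines alpha 0.025 with the shorter 1.5-year timeline in the text. Appendix 4 uses three periods, and that mismatch is a separate issue. On Appendix 4's own events, alpha alone moves power from about 0.80 to 0.70–0.72.

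**What to change.** In Statistical analysis, replace the blanket threshold with:

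- Each pairwise comparison of attainment of at least three targets is tested two-sided at 0.01.
- For first diabetes-related events, TEC vs UC is tested two-sided at 0.025. EC vs UC is tested at 0.05 only if TEC vs UC is significant.
- All other comparisons are reported with nominal 95% confidence intervals. This includes RAS inhibitor use, unless the sponsor declares it a separate primary test and gives it a level.

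**Cost.** The change is a short replacement text and needs no more patients for the primary, since the weakest pair keeps 99.5% power. The event levels stay as planned. The gate costs EC vs UC a little power: on Appendix 4's timeline (Schoenfeld; TEC vs UC power 0.965 at 0.025 with 136.7 events) it lies between 0.803 + 0.965 − 1 = 0.768 and 0.803.

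If the sponsor prefers to test both event comparisons at 0.025 with no order, the EC vs UC power should be restated as about 70–72% on Appendix 4's 148.4 events.
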